## Abstract

**Background:**

Play is a fundamental aspect of children’s development, fostering their cognitive, social, and emotional growth. However, children with intellectual disability (ID) experience limitations in their ability to engage in play, which can impact their relationships with caregivers. Parents of children with ID face heightened stress and reduced playfulness in their interactions with their children. Existing early interventions have primarily focused on behavioral parent training programs to manage challenging child behaviors, lacking a direct and positive approach to enhancing parent-child play interactions and relationships.

**Objective:**

This study aims to develop, implement, and evaluate ‘Just Play’(JP), a creative arts therapies-based dyadic early intervention to enhance the quality of mother-child interactions through positive playful engagement.

**Methods:**

A mixed-methods randomized controlled trial will be conducted with 60 mother-child dyads (children aged 3–7 with a prior ID diagnosis). Participants will be randomly assigned to either the JP dyadic intervention or to psycho-educational parent counseling control group. Quantitative data will include measures of emotional availability, mother and child playfulness, and the level of interpersonal synchrony between mothers and their children at baseline and post-intervention. Additionally, qualitative interviews with a subset of mothers in the JP group will be conducted at post-intervention and two-month follow-up to explore their experiences and identify the best practices of the intervention.

**Results & Implications:**

This study will provide empirical evidence on the effectiveness of JP dyadic intervention in strengthening positive mother-child relationships in families of children with ID. Findings will inform future early intervention strategies, contributing to evidence-based guidelines for practitioners working with children with ID while emphasizing the unique contribution of creative arts therapies to this population.

**Trial registration:**

ClinicalTrials.gov, registered August 6, 2024 (NCT06541782 || https://clinicaltrials.gov/study/NCT06541782).

## Background

Play is a universal activity through which children acquire early knowledge of the world and promote their cognitive, linguistic, social, and emotional development [1,2]. Contemporary developmental theories conceptualize play as an intrinsically motivated, voluntary, and pleasurable activity that is driven by joy and engagement rather than external goals [3–5]. Major theorists, including Piaget, Vygotsky, and subsequent developmental scholars, have emphasized play as a primary context for learning, symbolic representation, self-regulation, and social understanding across childhood [1–4].

The development of children’s play parallels the progression of their general development [4]. The first stage of sensorimotor play, appears in early infancy, and involves sensory exploration and bodily motor coordination and movement [1]. This is followed by object play, in which children use objects functionally and symbolically, and subsequently by pretend play and social play, developmental milestones associated with abstract thinking, flexible cognition, and advanced language skills [1,5]. Although play skills typically increase in complexity with development, play trajectories are non-linear and shaped by individual differences and environmental interactions [6]. Furthermore, while most children acquire play skills through observations and responsive interactions with caregivers, children with disabilities may need intentional interventions to develop certain play abilities [7].

Children with intellectual disability (ID) constitute a heterogeneous group characterized by significant limitations in intellectual functioning and adaptive behavior with onset in the developmental period. These limitations affect multiple developmental domains including language, motor skills, communication, and perception, and substantially constrain opportunities for play, exploration, and social engagement [6,7]. Research on play development indicates that children with ID exhibit less sophisticated play patterns compared to their typically developing (TD) peers, often resembling those observed in much younger children. Specifically, children with ID demonstrate a predominance of sensorimotor and physical forms of play [8,9]. Studies examining play preferences among children aged 3–7 years further reveal that children with ID show stronger preferences for sensorimotor rough-and-tumble play and object exploration, alongside lower preferences for symbolic and pretend play relative to TD children [10]. Within sensorimotor play, limited motor coordination frequently constrains performance, leading children with ID to favor physical activities that require minimal precision and coordination [9]. These motor challenges, along with other difficulties, influence their object play, which tends to be repetitive and less elaborated, characterized by non-exploratory behaviors such as mouthing, pounding, or squeezing objects [9]. Symbolic play emerges more slowly in this population, resulting in pretend play that is less imaginative, elaborated and flexible compared to TD children [9,11,12].

Children with ID experience delays in the development of their social skills [11], and this is reflected in their social play: Research shows children with ID have difficulties in maintaining cooperative play with others, initiating or joining play, taking turns, or sharing toys [13,14]. Interestingly, familiar play activities were found to facilitate higher levels of social interaction in children with ID than more demanding novel tasks [15]. These deficiencies profoundly influence the social development of children with ID and may lead to long-lasting emotional and behavioral issues that affect not only the children but also their parents, affecting the early stages of their relationships [12,16].

Rearing a child with ID can be demanding, with research suggesting that parents of children with ID are at a high risk of encountering elevated stress levels, social isolation and attenuated psychological well-being [12]. The parenting experience can be further challenged by the behavioral and emotional difficulties that often emerge in children with ID. Indeed, the risk of developing behavior disorders among children with developmental disabilities, such as ID, is three to four times higher than among TD children, placing them at a heightened risk for the emergence of comorbid psychopathology [17,18]. These challenges between parents and children with ID manifest themselves in lower levels of parental emotional availability (EA) [19] and parent-child interpersonal synchrony (IPS) [20], two constructs that have been extensively researched and shown to be central to the parent-child relationship and to child development in general [21–23].

EA refers to the dyad’s capacity to establish and maintain a healthy relationship, focusing on the parent’s ability to understand and respond to the child’s needs [24]. Emotional transactions between parents and children are evaluated according to six categories: parental sensitivity, parental structuring, parental non-intrusiveness, parental non-hostility, child responsiveness, and child involvement. High levels of parental EA are associated with secure attachment, positive parent-child relationships, and favorable child outcomes, including emotional regulation and social development [24]. Parent-child IPS refers to the dynamic and reciprocal adaptation of movements and behaviors, both verbal and non-verbal, between the parent and child, such as postures, gestures, breathing patterns, vocalizations, and facial expressions [22]. IPS in turn lays the foundation for the child’s ability to form intimate relationships in the future and thereby plays a pivotal role in developing self-regulation, positive self-esteem, empathy, and peer competence [20,23]. Parents and children with ID tend to share fewer moments of joint attention and engagement than TD children, displaying fewer patterns of symmetrical behavior and lower parent-child synchrony [25]. Studies also suggest that mothers of children with ID tend to exhibit fewer sensitive responses and engage in more intrusive and directive behaviors, often relying on commands and physical control [26,27]. Thus, recent research on children with ID emphasizes the need for early interventions that focus on fostering positive parent-child relationships, given the unique challenges that parents of children with ID may encounter and the critical role that the parent-child relationship plays on shaping the child’s developmental and emotional outcomes [17,28,29].

While intervention programs for children with ID have traditionally focused on addressing their developmental challenges, recent studies have shown more early intervention programs that target parenting and dyadic communication skills in this population [29]. Among the most salient programs for behavioral parent training is the Incredible Years Parent Training, adapted for use with parents of preschool children with mixed developmental delays (IYPT-DD) [30]. The program is based on 12 weekly group sessions for parents and employs discussion, video modeling, role-playing, and psycho-education on raising a child with developmental delays, with a focus on fostering positive parent-child interactions. The IYPT-DD has been shown to be efficacious in reducing negative parent-child interactions and child behavior problems, providing evidence that parenting processes can improve problematic behaviors in young children with developmental delays [31]. Similar behavioral parent training programs that focus on reducing child undesired behaviors include the Stepping Stones Triple P [32] and Parent-Child Interaction Therapy [33], with the former being a parent training program performed in a group format and the latter being performed in an individual format and adapted for parents of children with both ID and oppositional defiant disorder [32–34]. Both of these programs demonstrated success in mitigating children’s challenging behaviors and negative parenting behaviors, drawing on principles guided by applied behavior analysis and providing parents with behavior management strategies that reinforce children’s positive conduct [34]. While these interventions offer evidence that constructive interaction patterns between parents and children with ID can be taught and favorably affect behavioral outcomes, they generally do not emphasize fostering positive and playful parent-child interactions, but rather focus on providing specific strategies for parents to deal with problematic behaviors of their children with ID. Instead of primarily addressing behavioral challenges, our proposed intervention centers on promoting joyful engagement and strengthening the parent-child relationship through play.

Parent-child play serves as an ideal context for parents to connect with their young children in a playful and joyful manner, building upon their shared history by incorporating additional positive experiences, thereby supporting their relationship and the children’s social and emotional development. Despite the verbal and cognitive barriers children with ID face, play offers them a medium through which they can express their emotions and inner world. Studies on the playfulness of children with ID have found the children’s playfulness to be lower than that of TD children [35,36]. Furthermore, early play interventions for children with ID have improved the children’s playfulness regardless of the severity of their disability, offering a promising direction given the contributions of play and playfulness to the children’s socio-emotional development [37].

Parental playfulness, a relatively understudied characteristic of parenting, is characterized by joyfulness, fun, and creativity and offers parents a unique opportunity to establish a positive communication approach with their children [38]. The only study on parental playfulness among parents of children with ID found them to exhibit lower levels of playfulness compared to parents of TD children. Furthermore, higher levels of parental playfulness were shown to serve as a protective factor against the development of behavior problems in these children [39]. Therefore, early dyadic interventions that focus on fostering playfulness among parents and children with ID may support their relationships as well as advance the children’s socio-emotional development, even preventing the development of behavior problems, a major challenge experienced by 30–50% of this population [12,40].

Creative Arts Therapies (CAT), “characterized by the clinical and evidence-informed use of the arts within a therapeutic relationship that relies on experiential and action-based interventions” [41] refer to a variety of methods including musical engagement, visual art, movement and dance, drama/theater, and expressive/creative writing. CAT can provide a fertile terrain for cultivating playfulness and engaging interactions in parents and children with ID, since these therapies are based on non-verbal, creative art-based techniques [41,42]. The unique characteristics of the CAT, the multi-sensorial exploratory experiences, creativity, imagery, and emotional self-expression can help foster interactions between parents and children with ID [41,43]. A recent scoping review of music, dance, and drama therapies for individuals with ID confirmed the positive effects of these therapies on physical, emotional, and cognitive components, as well as on the social skills of this population [44]. However, research on CAT interventions for children with ID and their parents is scarce, although CAT-based dyadic interventions provide significant benefit by fostering playfulness within parent-child interactions in children with ID, thus ameliorating their relationship.

### Study objectives

This study aims to develop, implement, and assess ‘Just Play’(JP) - a dyadic CAT-based intervention that emphasizes the inherent value of dyadic play as an end of itself, encouraging mutual play and enjoyment between children with ID and their mothers. By engaging in spontaneous play, dramatic and musical improvisation, singing, and dyadic movement in a nonjudgmental and pleasurable space, this study assumes that the dyads will enhance their relationship quality. The trial is a mixed-methods randomized controlled longitudinal study. The study aims to quantitively assess the effectiveness of the JP dyadic intervention to improve mother-child interactions in comparison to psycho-educational parent counseling. The study will examine whether mother and child playfulness serve as mechanisms of change, thereby enhancing the quality of their interactions. The qualitative assessment will explore the mothers’ perspective on participating in the intervention, pinpointing its essential characteristics for stimulating maternal playfulness and identifying its long-lasting potential gains on the daily dyadic interactions from the maternal perspective.

### Research questions

To what extent will the JP dyadic intervention increase the quality of mother-child interactions (as reflected in EA and IPS outcome measures) in comparison to the psycho-educational parent counseling group?To what extent will the JP dyadic intervention improve mothers’ and children’s playfulness in comparison to the psycho-educational parent counseling group?How do mothers of children with ID perceive the role of the JP dyadic intervention in shaping their relationships with their children?What intervention characteristics and practices do mothers find the most valuable in stimulating and cultivating playful mother-child interactions during the intervention sessions?

### Study hypotheses

Mothers and children from the JP intervention group will demonstrate greater improvements in mother-child interaction quality as measured by EA and IPS, compared to the psycho-educational parent counseling group.Mothers and children from the JP intervention group will show greater improvement in their playfulness outcome measures, compared to the psycho-educational parent counseling group.Participation in the JP dyadic intervention will contribute to an improvement in mothers’ and children’s playfulness, which consequently will mediate the increase in EA and IPS.

## Methods

### Study design

This mixed-methods RCT aims to compare between two conditions: JP dyadic intervention and psycho-educational parent counseling. The quantitative data assessing participants’ outcomes from both conditions will be collected at two-time points: before participation in either program and one week upon program completion. The qualitative data will be based on interviews with 12 mothers participating in the JP intervention condition and will be collected at two-time points: one week after participation in the JP intervention and a follow-up two months later. The qualitative component will examine mothers’ subjective experiences and meaning-making processes, with particular attention to how they interpret their engagement in the JP dyadic intervention. Incorporating a qualitative arm responds to recent calls for mixed-methods approaches that foreground participants’ lived experiences and perspectives, thereby enriching the evaluation of the intervention processes and outcomes [45]. This approach is especially pertinent for dyadic interventions, where relational dynamics and experiential change may not be fully captured by quantitative measures alone. The qualitative strand in this research is intended to provide in-depth understanding of the intervention experience and potential mechanisms underlying its effects, rather than reproducing between-group comparisons.

Fig 1 depicts SPIRIT schedule of enrollment, interventions, and assessments and Fig 2 depicts the study’s CONSORT flow diagram [46].

**Fig 1 pone.0349576.g001:**
[figure not shown]
SPIRIT Schedule of Enrollment, Interventions, and Assessments.

**Fig 2 pone.0349576.g002:**
[figure not shown]
CONSORT Flow Diagram.

### Participants

The study will include two groups of 30 dyads (total of 60 dyads), each consisting of a mother and her child between the ages of three and seven with a prior diagnosis of ID. The inclusion criteria require that children have a prior diagnosis of ID by a developmental pediatrician. Exclusion criteria include children with an additional primary diagnosis, such as autism spectrum disorder or sensory disorders like blindness or deafness. Participants will be recruited through special education preschools for children with developmental disabilities (which are separate from preschools for children diagnosed with ASD), and through flyers posted in social media groups for parents of children with ID.

### Sample size

Previous studies using pre/post EA total sum scores to compare the effectiveness of parent-child interventions [47,48] have reported medium to very large (0.5–1.17) effect size according to Cohen’s [49] criteria. The study is powered to detect a large between-group effect size of Cohen’s d = 0.8 in the primary outcome of change in EA total sum scores between baseline and post-intervention. With a significance criterion of α = 0.05 and power = 80%, the minimum sample size is n = 52 with n = 26 in each sample. Assuming drop-out does not exceed 10%, the aim is to recruit 60 families in total. Furthermore, given the nature of the study involving a short-term home-delivered intervention, n = 30 families in the JP intervention group seems to be a feasible yet significant number.

### Ethics approval and consent

The current study was approved by the ethics committee for the evaluation of research with human subjects of the Faculty of Social Welfare & Health Sciences, University of Haifa, Israel, approval no: 057/23, date of approval: 14 February 2023, and the ethics committee of the Head Scientist of the Israeli Ministry of Education approval no: 1347, date of approval: 10 September 2023. Parents will give written informed consent for their participation and their children’s participation in the study and publication of the results. Participant recruitment began February 22nd, 2024 and is currently ongoing.

### Study procedures

After initial contact and providing a comprehensive explanation of the study, the investigator recruiting participants will confirm that eligibility criteria have been met. Following the provision of written informed consent, eligible dyads will be randomly assigned to only one of the conditions – either the JP dyadic intervention or the psycho-educational parent counseling group, using an allocation ratio of 1:1. A permuted block randomization sequence (block size of 4) will be generated using Microsoft Excel. To ensure balance between the conditions, assignments within each block will be randomized using the = RAND() function. The final sequence will be locked into a static spreadsheet to maintain the integrity of the allocation. Participants will be aware of the condition they will participate in, and the study’s focus on the quality of the mother-child interaction in the assessment meetings. However, they will not be aware of the study design (that the psycho-educational parent counseling group was chosen as the control group).

After the randomization process, the baseline assessment meeting will be conducted at the participants’ homes. The assessment meeting will comprise a mother-child interaction protocol including four consecutive episodes: (a) 10 minutes of free play with a standardized set of toys; (b) 5 minutes of play with a doll and accessories; (c) 7 minutes of social play without toys; and (d) a 3-minute mutual movement activity accompanied by music. All interaction episodes will be video-recorded for subsequent coding. The dyads will then participate in the assigned intervention program. Upon completion of the intervention program, a post-intervention assessment will be conducted using the same mother-child interaction protocol and procedures as the baseline assessment.

In addition, qualitative interviews with a subset of mothers in the JP group will be conducted at post-intervention and two-month follow-up. As the study aims to provide in-depth understanding of the intervention experience and potential mechanisms underlying its effects on the mother-child interactions, the Interpretative Phenomenological Analysis (IPA) methodology was chosen to allow idiographic and phenomenologically grounded exploration of the mothers’ experiences. IPA guidelines recommend small, relatively homogeneous samples to permit detailed case-by-case analysis prior to cross-case interpretation [50]. Therefore, interviewing a subsample of 12 mothers from the intervention group will allow for sufficient experiential depth while maintaining analytic rigor consistent with IPA methodology. The mothers will be selected in a purposeful sampling process [50]. All eligible mothers who complete the JP intervention will be invited to take part in a qualitative part of the study immediately following completion of the intervention, and recruitment will continue until the target sample of 12 participants is reached. The interviews will be conducted in the mothers’ homes by a member of the research team who was not involved in intervention delivery. The post-intervention interview will be semi-structured and in-depth. The two-month follow-up interview will incorporate an Interpersonal Process Recall procedure, during which the mother and interviewer will jointly watch selected video excerpts from the intervention sessions and reflect on them [51,52]. All interviews will be audio-recorded and transcribed verbatim for qualitative analysis.

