### Mediation measures

Parental Playfulness Scale (PPS) [62] evaluates the parent’s playfulness. The PPS is a standardized observational video analysis tool that assesses parental creativity, imagination, humor, pretend play, and curiosity while playing with their children. The PPS is composed of three subscales: parent’s playfulness, following the child’s lead, and peer-like behavior rated on a 7-point Likert-type scale from 1 to 7, with a higher score signifying more playfulness. All scores are averaged into a single playfulness score for each parent. The PPS will be scored based on the video-recorded episodes of free play and play with a doll. The PPS has been shown to have high interrater reliability of 0.8 [38,63] and has been used to assess the playfulness of parents to children with ID [27].Test of Playfulness (ToP; version 4.2) [64] evaluates the child’s playfulness. The ToP is a standardized observational video analysis tool comprised of 30 items rated on a 4-point Likert-type scale from 0 to 3, evaluating the extent, intensity, and skill of the child at play, with a higher score signifying more playfulness. All scores are averaged into a single playfulness score for each child. The ToP will be scored based on the video-recorded episodes of free play and play with a doll. Studies have established the reliability and validity of the ToP determining goodness-of-fit according to the Rasch analysis model when used with children with ID [35,36], and has been used in previous intervention studies [37].

The outcome measures of EA, child playfulness (ToP), and parent playfulness (PPS) will be coded by blind and trained researchers. Interrater reliability will be determined by comparing 20% of the data to an additional blind and trained scorer using the interclass correlation coefficient [65] to establish consistency of independent ratings.

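### A constant, disclosed block size of 4 makes one third of allocations predictable to a recruiter who follows earlier assignments, and mixed undisclosed blocks for the remaining dyads would remove most of that certainty

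*Protocol article*

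**What the plan says.** All of the relevant text is in the article's Study procedures section, apart from the statement on coders.

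- **Sequence:** "A permuted block randomization sequence (block size of 4) will be generated using Microsoft Excel", "using an allocation ratio of 1:1". Within blocks, "assignments within each block will be randomized using the = RAND() function". No stratification is described, so there appears to be a single list.
- **Storage:** "The final sequence will be locked into a static spreadsheet to maintain the integrity of the allocation".
- **Enrolment:** after the study has been explained, "the investigator recruiting participants will confirm that eligibility criteria have been met". Then: "Following the provision of written informed consent, eligible dyads will be randomly assigned to only one of the conditions".
- **Masking:** "Participants will be aware of the condition they will participate in". Under Mediation measures, the emotional availability (EA), child playfulness and parent playfulness scores "will be coded by blind and trained researchers". No one else is described as blind.
- **Order of baseline:** the baseline home visit comes after randomisation.

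The Interventions section shows that the arms cannot be confused: home sessions with mother and child in one, online sessions with the mother alone in the other. Status and timeline reports 40 dyads recruited out of a planned 60.

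**The concern.** In a 1:1 block of 4, once two dyads have gone to one arm, the rest of the block is fixed. The fourth assignment is always fixed by the first three. With one list, one constant block size and openly delivered conditions, anyone who knows the block size and counts assignments can work this out. Locking the spreadsheet stops the sequence from being altered; it does not stop the next assignment from being predicted.

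The person best placed to act on a prediction is the one who speaks to families, explains the study and confirms eligibility. Foreknowledge could affect which family is approached next, when, and how warmly the study is presented. This needs no bad intent: home visits and video calls suit different families, which gives an ordinary practical reason to prefer one arm for a given dyad.

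At stake is the comparability of the two groups. Blind coding protects the measurement of EA, not the composition of the arms. The planned mixed model uses pre and post scores and names child gender and the VABS-3 score as covariates. That deals with part of a difference in starting level or severity, but not with a difference in maternal motivation or likely response.

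**Working it through.** **Inputs.** Block size 4, ratio 1:1, random order within block (Study procedures); 60 dyads planned (Sample size); 40 recruited (Status and timeline). The article gives no predictability figure to reproduce. Its sample size is not at issue: a two-sided t-test with d = 0.8, α = 0.05 and 80% power gives 25.52, so 26 per arm and 52 in total, as stated.

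**Certain allocations.** A block has 4!/(2!·2!) = 6 equally likely orders.

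- AABB and BBAA: the third and fourth assignments are known, 2 each.
- ABAB, ABBA, BABA and BAAB: only the fourth is known, 1 each.
- Mean per block: (2·2 + 4·1)/6 = 8/6 = 1.333.
- Share: 1.333/4 = 1/3. By position in the block: 0, 0, 1/3, 1.

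Over 60 dyads (15 blocks) this is 15 × 1.333 = 20 expected, with a possible range of 15 to 30. Over the 20 dyads still to come (5 blocks) it is 5 × 1.333 = 6.7, with a possible range of 5 to 10.

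**Best guess.** The recruiter always guesses the arm with more places left in the block, and tosses a coin when they are equal.

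- Position 1: 1/2.
- Position 2: 2/3.
- Position 3: the first two agree with probability 1/3 (then certain) and differ with probability 2/3 (then 1/2), so 1/3 + 1/3 = 2/3.
- Position 4: 1.
- Mean: (1/2 + 2/3 + 2/3 + 1)/4 = 17/24 = 70.8%.

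**Alternatives.** Fixed blocks were enumerated exactly. Mixed blocks were simulated for 60 dyads, with a recruiter who knows the possible sizes and sees every assignment but does not know the size of the current block.

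| Scheme | Certain | Best guess correct |
|---|---|---|
| Fixed 4 (as planned) | 33.3% | 70.8% |
| Fixed 6 | 25% | 68.3% |
| Fixed 8 | 20% | 66.6% |
| Mixed 4/6 | about 5.5% | about 69% |
| Mixed 4/6/8 | about 2.4% | about 68% |

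Limiting the simulation to 20 dyads from a known block boundary gives about the same shares. For those 20, certain allocations fall from about 6.7 to 20 × 0.055 = 1.1 or 20 × 0.024 = 0.5. Mixing sizes therefore removes most of the certainty but little of the advantage in guessing. A larger fixed block removes much less of the certainty.

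**The case against.** The strongest reply is that the one-third figure describes what a fully informed recruiter could know, not a leak that the article documents. A reader might infer that every past allocation is visible to the whole team, or that the recruiter does know the coming arm. The text supports neither. It says that participants know their own condition; it does not say that the recruiter follows the sequence, and the two interventions are given one family at a time by different professionals. This stands, and the point is conditional for that reason.

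A reader might also infer that publishing the block size exposed all 60 dyads. It could affect only the 20 or so not yet recruited. For the first 40, any risk depends on what the team already knew. Nor does the article's silence on who holds the list show that concealment is absent; an article may leave that to the full protocol. The point rests on the stated constant block size. A concealed list does not by itself prevent prediction from a known block size and known earlier assignments.

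The room for steering is limited. Entry depends mainly on age and a diagnosis made before recruitment, and assignment follows written consent. Both help, but a prediction can be made before consent is sought, so the timing and manner of approach remain open.

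Finally, small fixed blocks are a recognised way to keep a 60-dyad trial balanced, which is the aim the article gives. Mixed small blocks keep nearly all of that balance.

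**Conclusion.** The concern holds as an avoidable weakness, not as evidence of bias. Under the stated scheme, a recruiter who knows the block size and follows earlier assignments can be certain of one third of allocations, about 7 of the 20 still to come, and can guess 71% correctly. The arithmetic is exact. It assumes a single unstratified list and that the recruiter has both pieces of knowledge, which the article neither states nor excludes. No effect on the EA comparison can be estimated from the document, and nothing in it shows that selection has taken place. Sample size and power are not affected. The change is worth making because it is cheap and a third of the sample can still benefit.

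**What to change.** 1. At the next block boundary, replace the rest of the list with one built from randomly mixed block sizes (for example 4 and 6, or 4, 6 and 8) that are not disclosed to the recruiter. The boundary is dyad 41 if exactly 40 have been randomised, since 40/4 = 10 full blocks; otherwise complete the current block first.
2. Because guessing remains possible at 68–69%, make sure that the recruiter sees neither the list nor the running order of assignments. If the full protocol already provides for this, confirm it.
3. For the remaining dyads, assign after the baseline assessment, reversing the order now stated. In a trial where mothers know their condition, this ensures that baseline behaviour is recorded before they can know it. It is a separate gain and does not itself reduce predictability.
4. Document the change and its date, and report it with the results.

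**Cost.** A new list and a procedural note. The last block may be cut short. With 20 dyads to go, a cut block of 4 or 6 leaves the arms at most 2 apart (31:29), and a block of 8 cut at its midpoint at most 4 apart (32:28). Either has a negligible effect on power. The first 40 dyads were to be assigned under the fixed blocks and baseline order stated in the article, so the report should describe both procedures.
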